## Abstract

**Background:**

Mood and anxiety disorders are highly prevalent and have a large impact on the lives of the affected individuals. Therefore, optimal treatment of these disorders is highly important. In this study we will examine the effectiveness of a stepped care program for primary care patients with mood and anxiety disorders. A stepped care program is characterized by different treatment steps that are arranged in order of increasing intensity.

**Methods:**

This study is a randomised controlled trial with two conditions: stepped care and care as usual, whereby the latter forms the control group. The stepped care program consists of four evidence based interventions: (1) Watchful waiting, (2) Guided self-help, (3) Problem Solving Treatment and (4) Medication and/or specialized mental health care. The study population consists of primary care attendees aged 18–65 years. Screeners are sent to all patients of the participating general practitioners. Individuals with a Diagnostic and Statistical Manual of mental disorders (DSM) diagnosis of major depression, dysthymia, panic disorder (with or without agoraphobia), generalized anxiety disorder, or social phobia are included as well as individuals with minor depression and anxiety disorders. Primary focus is the reduction of depressive and anxiety symptoms. Both conditions are monitored at 8, 16 and 24 weeks.

**Discussion:**

This study evaluates the effectiveness of a stepped care program for patients with depressive and anxiety disorder. If effective, a stepped care program can form a worthwhile alternative for care as usual. Strengths and limitations of this study are discussed.

**Trial Registration:**

Current Controlled Trails: ISRCTN17831610.

## Background

Depressive and anxiety disorders are highly prevalent [1]. Currently, depressive disorders are the fourth disorder worldwide in terms of disease burden, and will be the disorder with the highest disease burden in high-income countries by 2030 [2]. Anxiety and depression can cause serious functional impairment, reduced quality of life [3,4], high levels of public service usage and huge economic costs [5,6]. Comorbidity is high among psychiatric disorders in general [1]. Almost half of the people who have ever suffered from a psychiatric disorder have had more than one. Comorbid anxiety is the rule rather than the exception with up to 60% of the patients with major depressive disorder also suffering from an anxiety disorder [7]. Because of this high comorbidity and the difficulties in distinguishing the two disorders without extensive diagnostic interviews, this study includes individuals with depressive disorders as well as with anxiety disorders.

There are ongoing discussions regarding the effectiveness of the management of common mental health problems in general practice settings. Both anxiety disorders and depression can be treated effectively by pharmacotherapy as well as psychotherapy [8-15]. Although evidence based clinical guidelines are available, initiation and adherence to effective treatment are usually poor [16-19]. Mood and anxiety disorders often remain unrecognised and therefore untreated in primary care [20]. Furthermore, it has been demonstrated that even when depression has accurately been recognized, still only few patients receive adequate care [19]. According to several studies [21-23] many patients receive antidepressants immediately after the diagnosis was determined, however, only few patients receive adequate dosage and duration of (antidepressant) medication. Approximately 30% of depressed primary care patients stop using antidepressant medications within the first month of treatment, while only 40% reach the recommended therapeutic dosage of antidepressant medication [24]. It is also important to note that the majority of primary care patients prefer psychotherapy as a treatment [25]. Clearly, the gap between research findings and clinical practice is wide in the management of depression in primary care [26].

Through its objective of initiating interventions at the right time and as adequately as possible, the stepped care model could provide a solution for the problem of applying effective, evidence based care for depression and anxiety. Care is offered not earlier or more intense than necessary and not later or less intense than needed [27,28]. In a stepped care model, all patients start with an evidence-based treatment of low intensity as a first step. Progress is monitored and patients, who do not respond adequately can 'step up' to a subsequent treatment of higher intensity [29]. An important feature of the stepped care model is that the model is self-correcting. Self-correcting means that the results of treatments and decisions about treatment provisions are monitored systematically and where necessary changes are made ('stepping up') if current treatments are not achieving significant health improvement [27]. A care manager coordinates a stepped care program, preferably a paraprofessional who supports the primary care clinic handling psychiatric problems. In The Netherlands the most likely candidate for this role is a psychiatric nurse. This care manager coordinates the monitoring of the patients, provides the first treatments in the stepped care model and refers the patient to the appropriate mental health care specialist if necessary.

Although the stepped care model seems to be a promising care model [27-30] to increase the effectiveness and efficiency of the mental health system, its effectiveness compared with care as usual (CAU) has not been studied yet [27-29]. We will describe the protocol of a study on the (clinical) effectiveness of this program versus care as usual with patients who are diagnosed with a minor or major mood and/or anxiety disorder.

## Methods

### Study design

This study is a randomised controlled trial. We recruit patients by screening all patients of the participating GPs during an inclusion period of 1,5 years. All patients with a positive screen for depression and/or anxiety are screened again after 4 to 6 weeks. Those with a second positive screening (baseline) are contacted by telephone for a diagnostic interview. During this interview all in- and exclusion criteria are checked. Those who are eligible for participation are being asked for informed consent to participate in the study. All patients who give informed consent are subsequently randomised to either (1) stepped care or (2) care as usual. All patients are asked to fill out questionnaires again after 8, 16 and 24 weeks. The study protocol, information brochure and informed consent are approved by the Medical Ethics Committee of the VU University Medical Center (registration number 2006/248).

### Inclusion and exclusion criteria

We include adults aged 18 – 65 years with one or more of the following DSM-IV diagnoses: major depression (single episode or recurrent), dysthymia, panic disorder (with or without agoraphobia), social phobia or generalized anxiety disorder, including comorbid diagnoses. We also include patients with a minor depression or a minor anxiety disorder. We use the DSM-IV research criteria to define minor depression. The main difference between the criteria of minor and major depression is that for minor depression only two to four out of nine symptoms have to be present, of which at least one has to be a core symptom (depressed mood or markedly diminished interest or pleasure in all, or almost all, activities). As there are no DSM criteria, we define a minor anxiety disorder as a score of 12 or more on the Hospital Anxiety and Depression Scale [31] and dysfunctioning in daily life (household, work and/or social relations). Exclusion criteria are psychotic or bipolar disorder, current (< 2 months) treatment (medical/psychotherapy) for psychological problems, prominent suicide ideation, severe alcohol problems (> 20 on the Alcohol Use Disorders Identification Test (AUDIT)[32], no motivation for treatment and insufficient knowledge of the Dutch language.

### Recruitment

#### Recruitment of GPs

In the present study we collaborate with two mental health centers in Amsterdam (GGZ inGeest and Mentrum). Both of these mental health centers employ psychiatric nurses and psychologists, who work for a few hours per week in a GP practice. Usually, GPs refer patients to these psychiatric nurses/psychologists for short-term treatments. First we want to approach psychiatric nurses and psychologists and secondly we want to invite the corresponding GPs to collaborate in this study.

#### Recruitment of patients

Patients are recruited by screening all patients of the participating GPs during the inclusion period of 1,5 year. All patients with a positive screen for depression and/or anxiety are assigned to a watchful waiting period of 4 weeks. After 4 weeks every patient is screened again to exclude the patients who recover spontaneously. This second screener is the baseline questionnaire (T0) and is sent to each patient together with general information about the project and an informed consent form. Two weeks later the patients are approached for a diagnostic interview (Composite International Diagnostic Interview: CIDI) [33] by telephone to check for in- and exclusion criteria. Patients who meet the inclusion criteria *and *return their informed consent are randomised.

### Randomisation

Randomisation takes place at an individual level. Patients are randomised into two groups, stratifying by care manager and using blocks of 4 to prevent overburdening the care managers. An independent researcher not involved in the current project uses computer generated block randomisation to produce sealed envelops. After every inclusion the researcher opens a sealed envelop.

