### Intervention

The stepped care intervention consists of four steps: *(1) Watchful waiting*. Patients with mood and anxiety disorders often recover spontaneously over time [34]. In the first step the patients receive no treatment for four weeks. In this project, only patients who still show symptoms of anxiety/depression after the watchful waiting period, are included. They start with (2) *Guided self-help*. Guided self-help starts with one 30 minute session with a care manager. This session enables the care manager to check exclusion criteria (e.g., severe psychopathology), to give psychoeducation (e.g., advice on lifestyle) and to explain the self-help interventions. In this study we have two different self-help interventions available. The first is a generic intervention based on problem solving treatment, which aims at patients with symptoms of mood and/or anxiety disorders. The Dutch version of self-examination therapy is called "*Alles onder controle*" and is available as a book and through the Internet. The patient can choose to get feedback by email or by telephone. In this study feedback is provided by coaches (members from the research group) from the VU University. The focus of the feedback is to guide the patient through the intervention by motivating and activating them. When patients send their assignments to their coach, they receive feedback within 3 working days. The second self-help intervention is specifically aimed at patients with phobias and is based on exposure therapy. In this course patients first have to make a list of all the situations that provoke anxiety and put them in order of intensity. Next they have to make a plan to practice exposure to these situations based on this anxiety hierarchy. This course takes six weeks to complete and is only available as a book. Feedback is therefore provided by telephone. During the first session, the care manager and the patient together decide which self-help course is most suitable. Patients who do not recover using self-help treatment start with (3) *Problem Solving Treatment (PST)*. PST is a short psychological intervention, 5 sessions of 45 minutes each, provided by the care manager [35]. The treatment protocol is based on '*Problem-solving treatment for anxiety and depression: A practical Guide*' by Laurence Mynors-Wallis [36]. Recent studies show that PST is an effective treatment for major depression as well as for more general, emotional disorders containing depressive and anxiety symptoms [35,37-42]. Training in PST was given by a problem solving treatment expert in a two-day course followed by weekly group supervision sessions. Patients who are unresponsive to this treatment will proceed to the last step of the stepped care program (4) *Pharmacotherapy and/or specialized mental health care*. In case patients do not recover from PST they have one more session with the care manager to discuss the next step: either pharmacotherapy or more specialized mental health care. In case a patient chooses pharmacotherapy, the care manager sets up an appointment for the patient with the GP. In case the patient chooses specialized mental health care, the care manager sets up an appointment with a mental health care specialist.

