### Sample Size

A meta-analysis on the effects of psychological treatment on patients with sub-clinical depression shows an effect size of 0.40. Based on a power of 0.80 in a two-tailed test and an alpha of 0.05, we need 100 patients in each condition. Therefore, the total sample size is set at 200.

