### Statistical Analysis

All analyses will be conducted according to the intention-to-treat principle. All respondents who have been randomised will be included in the analyses examining the effects of the intervention. Missing data will be imputed using regression imputation. The effectiveness of the stepped care program is measured via the primary outcomes: the HADS (anxiety) and IDS (depression). It is useful to know not only wether the effectiveness is statistically significant, We will use Cohens' *d *[71] to measure the size of the effect. Furthermore, GEE-analysis will be used to examine differences in speed of recovery between the two groups [72]. Additionally, we will report the percentage of patients who have recovered at the moment of the last assessment. In order to do so we will calculate the relative risk.

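### The sample size makes no allowance for stepped-care patients sharing care managers: 100 per arm gives about 0.80 power only if patients are independent, and the article does not say whether the analysis models care manager

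*Protocol article*

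**What the plan says.** The Randomisation section of the protocol article states: "Randomisation takes place at an individual level". It continues: "Patients are randomised into two groups, stratifying by care manager and using blocks of 4 to prevent overburdening the care managers".

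The Intervention section gives care managers a direct part in the stepped-care arm. They hold one opening session before guided self-help, provide problem solving treatment ("PST is a short psychological intervention, 5 sessions of 45 minutes each, provided by the care manager"), and hold one further session on the next step with patients who have not recovered. Feedback during self-help comes from research-group coaches. Under Exceptions, patients with extreme dysfunctioning go straight to step 4. Under Care as Usual, control patients are assigned no care-manager treatment but may seek care themselves.

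The Sample Size section states: "A meta-analysis on the effects of psychological treatment on patients with sub-clinical depression shows an effect size of 0.40". It then states: "Based on a power of 0.80 in a two-tailed test and an alpha of 0.05, we need 100 patients in each condition", and "Therefore, the total sample size is set at 200". It mentions no ICC, cluster size or design effect.

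The Statistical Analysis section names IDS and HADS as primary outcomes and adds that "GEE-analysis will be used to examine differences in speed of recovery between the two groups". It does not mention care managers.

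**The concern.** Each care manager treats several stepped-care patients, so outcomes in that arm may be correlated within care manager. By design the control arm has no matching source of correlation. This is a partially nested design. Stratifying by care manager balances differences that affect both arms of a stratum, such as the practice population. It does not remove differences in how well each care manager delivers the programme, because those act only on treated patients.

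Two things are at stake. The first is whether 200 patients give the stated power. The second is whether the primary comparison has a valid standard error as evidence about a programme run by ordinary care managers. The Discussion claims that kind of relevance, and it also acknowledges that treatment integrity is hard to maintain with staff not hired for research.

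**Working it through.** **Inputs from the protocol article.** d = 0.40 (so SD = 1), two-sided alpha 0.05, power 0.80, 100 per arm.

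**Assumed inputs, not in the article.** 5, 10 or 20 care managers with equal caseloads, so m = 20, 10 or 5 stepped-care patients each; delivery ICC of 0.02 to 0.05, with 0.01 also shown.

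**Step 1: reproduce the stated figure.** With independent patients, n per arm = 2 × (1.960 + 0.842)² / 0.40² = 98.1, so 99. The t-test version gives 99.08, which rounds up to 100. At 100 per arm, SE = √(2/100) = 0.1414 and power = Φ(0.40/0.1414 − 1.960) = Φ(0.868) = 0.807 (0.804 by t-test). The figure reproduces with no design effect.

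**Step 2: how much slack there is.** Let DE be the design effect in the stepped-care arm. Power of 0.80 at 100 per arm requires (1 + DE) × (1.960 + 0.842)² / 0.40² ≤ 100, which gives DE ≤ about 1.04. Since DE = 1 + (m − 1) × ICC, that limit is reached at an ICC of about 0.01 with m = 5, or 0.004 with m = 10.

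**Step 3: clustering in the stepped-care arm only.** SE = √((1 + DE)/100) and power = Φ(0.40/SE − 1.960). If the analysis ignored this clustering, two-sided type I error = 2 × [1 − Φ(1.960 × 0.1414/SE)].

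Worked case, 10 care managers and ICC 0.05: DE = 1 + 9 × 0.05 = 1.45; SE = √(2.45/100) = 0.1565; power = Φ(2.556 − 1.960) = 0.724; SE ratio = 0.1565/0.1414 = 1.107; type I error = 0.077.

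| Care managers (m) | ICC | DE | Power | Type I error if ignored |
|---|---|---|---|---|
| 20 (5) | 0.02 | 1.08 | 0.792 | 0.055 |
| 20 (5) | 0.05 | 1.20 | 0.769 | 0.062 |
| 10 (10) | 0.02 | 1.18 | 0.773 | 0.060 |
| 10 (10) | 0.05 | 1.45 | 0.724 | 0.077 |
| 5 (20) | 0.02 | 1.38 | 0.737 | 0.072 |
| 5 (20) | 0.05 | 1.95 | 0.644 | 0.107 |

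At ICC 0.01 the power is 0.80, 0.79 and 0.77 with 20, 10 and 5 care managers. All of these are large-sample normal approximations.

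**Step 4: the opposite case.** Suppose the only care-manager variation is shared by both arms, with ICC 0.05. It cancels from the contrast within strata, so the true SE is √(1 − 0.05) = 0.975 times the unadjusted SE. With strata modelled, SE = √(2 × 0.95/100) = 0.1378 and power = Φ(0.40/0.1378 − 1.960) = 0.83. Leaving care manager out would then make the standard error too large.

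**The case against.** A reader might infer that the planned GEE treats all 200 patients as independent, so that standard errors are certainly too small and the type I error certainly exceeds 0.05. The article does not support that. It leaves the clustering unit, the working correlation and the covariates of the GEE unstated, and an article may leave these to a full analysis plan. Step 4 also shows that the direction of any error depends on which kind of care-manager variation dominates.

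Other points weigh against a large effect:

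- **Exposure is partial.** Step 2 involves one 30-minute session, with the feedback given by coaches. Problem solving treatment goes only to patients who have not recovered, and the most impaired patients bypass it.
- **Delivery is partly standardised.** Care managers follow a treatment protocol, take a two-day course and attend weekly group supervision.
- **Control patients may reach the same providers.** The section on recruiting GPs says that referral to these nurses and psychologists is usual practice, and controls may seek care. To that extent provider effects are shared and partly cancel.
- **The size rests on assumptions.** The ICC and the number of care managers are not in the article. The low end of the range costs almost nothing, and nothing in the text supports pairing 5 care managers with ICC 0.05.

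All of this stands. It limits the likely size and rules out a claim that the analysis is wrong as written. It does not supply the allowance missing from the Sample Size section, which fixes both the power and the number of patients.

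**Conclusion.** The sample size makes no allowance for care-manager clustering, and the stated power holds only for independent patients. Under delivery ICCs of 0.02 to 0.05 in the stepped-care arm only, power is about 0.79 to 0.77 with 20 care managers, 0.77 to 0.72 with 10 and 0.74 to 0.64 with 5. Partial exposure makes the lower ICCs more plausible, so with 10 to 20 care managers the loss is probably modest.

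On the analysis, the conclusion is conditional. If care manager is left out, shared variation makes the standard error too large and treatment-specific variation makes it too small. Type I error of about 0.055 to 0.107 applies only if the treatment-specific part alone exists, over the same assumed range. The net direction cannot be settled from the article.

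**What to change.** 1. State that care manager, as the randomisation stratum, is included in the IDS and HADS models.
2. Allow a care-manager random effect in the stepped-care arm, with small-sample degrees of freedom, as the main analysis or as a sensitivity analysis.
3. In the Sample Size section, restate the power at 100 per arm for the actual number of care managers over a range of ICCs, for example 0.01 to 0.05, labelled as assumptions.

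This needs wording and one short calculation. It needs no extra patients and no new data, because care manager is already known for every patient as the stratum. The downside is somewhat wider intervals. If there are few care managers, the variance component will also be poorly estimated; in that case the random-effect model serves better as a sensitivity analysis beside a model adjusted for the stratum.

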#### Care as Usual

Patients randomised to the 'care as usual' will be informed about this outcome. They are informed that they can choose to find (mental) health care and are allowed to discuss this with their GP.

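### A constant block size of 4 within each care manager, in an open trial, leaves up to one third of allocations predictable to anyone who knows the stratum's history; varying the size is a cheap improvement

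*Protocol article*

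**What the plan says.** All references are to the protocol article.

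- **Scheme (Randomisation).** "Randomisation takes place at an individual level", "stratifying by care manager and using blocks of 4 to prevent overburdening the care managers". One block size is given, and the reason for it is workload. Nothing is said about varying it or withholding it.
- **Concealment (Randomisation).** "An independent researcher not involved in the current project uses computer generated block randomisation to produce sealed envelops". Then: "After every inclusion the researcher opens a sealed envelop". The text does not say whether this is the independent researcher or a member of the trial team.
- **Open treatment.** "Patients randomised to the 'care as usual' will be informed about this outcome" (Care as Usual). In the stepped care arm, the care manager meets the patient at the start of guided self-help, and "feedback is provided by coaches (members from the research group) from the VU University" (Intervention).
- **Entry.** The exclusions end with "no motivation for treatment and insufficient knowledge of the Dutch language" (Inclusion and exclusion criteria). Table 1 lists motivation as a telephone item at baseline and names no instrument for it. Patients are randomised once they meet the criteria and have returned consent (Recruitment of patients).
- **Ratio.** It is not stated under Randomisation. Equal arms are inferred from Sample Size: "we need 100 patients in each condition".

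**The concern.** Sealed envelopes stop someone from reading the next allocation. They do not stop someone from working it out. With a constant, known block size, the end of each block follows from the allocations already made in it. Because each care manager is a separate stratum and treatment is open, that history builds up visibly, one stratum at a time.

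If a person who influences inclusion had the history, they could, knowingly or not, judge a borderline patient's motivation, or time an inclusion, in the light of the arm that comes next. The arms could then differ at entry. Intention-to-treat analysis does not repair this, because it protects the comparison after randomisation and not the choice of who enters it.

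**Working it through.** **Inputs.** Block size 4 within care manager (Randomisation); 1:1 ratio, inferred from 100 per condition; 200 patients in total (Sample Size). The number of care managers is not given and is varied below as an assumption.

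**The plan's own figure.** The article gives no figure for predictability. Its sample size reproduces: effect size 0.40, two-sided alpha 0.05 and power 0.80 give 99 per arm by the normal formula and 99.08, rounded up to 100, by the t-test. It is used here only for the ratio and the total.

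**Step 1: certain allocations in a complete block.** There are six equally likely sequences: AABB, ABAB, ABBA, BAAB, BABA, BBAA. A position is certain when one arm is already used up in the block.

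| Position | Probability that it is certain | Probability that the best guess is right |
|---|---|---|
| 1 | 0 | 1/2 |
| 2 | 0 | 2/3 |
| 3 | 1/3 (first two alike) | 1/3 × 1 + 2/3 × 1/2 = 2/3 |
| 4 | 1 | 1 |

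- Certain share: (0 + 0 + 1/3 + 1) / 4 = 1/3 = 33.3%. Of 200 patients: 200 / 3 ≈ 67, if every block fills.
- Best guess (the arm that is behind): (1/2 + 2/3 + 2/3 + 1) / 4 = 17/24 = 70.8%, against 50% by chance.

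**Step 2: incomplete last blocks.** Spreading 200 patients at random over an assumed number of care managers (simulation) gives:

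| Care managers (assumed) | Certain share | Patients of 200 |
|---|---|---|
| 5 | 32% | 0.32 × 200 = 64 |
| 10 | 31% | 0.31 × 200 = 62 |
| 20 | 29% | 0.29 × 200 = 58 |
| 40 | 25% | 0.25 × 200 = 50 |

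So 67 is an upper bound.

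**Step 3: the alternative.** Take blocks of 4 and 6 chosen at random, 20 patients per stratum, and a guesser who knows which sizes are in use but not their order. By simulation, certain allocations fall to about 6% (0.06 × 200 = 12 patients). The best guess is still right about 69% of the time, because the arm that is behind remains the better bet. The largest imbalance within a care manager is half the largest block: 4 / 2 = 2 now, 6 / 2 = 3 under the alternative.

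**The case against.** The strongest reply is that nobody in the article is shown to have both the history and a say over inclusion.

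- **Who includes patients.** The interviews are described in the passive voice, and the section on the diagnostic interview speaks only of trained interviewers. The person who opens the envelopes may be the independent researcher named in the sentence before. A reader might infer that the research group interviews patients, includes them and opens the envelopes. The article does not say so.
- **Who knows the history.** Coaches from the research group see only the stepped care patients whom they coach. Patients with extreme dysfunctioning go straight to the fourth step and bypass self-help. Nothing says that coaches see care-as-usual allocations or their order. Care managers see their own stepped care patients, but the article gives them no role in inclusion before randomisation.
- **Room for judgement.** It is narrower than the list of exclusions suggests. Diagnoses come from a structured interview (CIDI), suicide risk is assessed with the MINI suicide instrument, and dysfunctioning is the patient's own WSAS rating. Timing depends largely on mailed screening and on the patient's return of the consent form.
- **Repair.** IDS and HADS are measured before randomisation, so imbalance on the primary measures can be seen and adjusted for.
- **Safeguards.** The list is made independently, and envelopes are opened only after inclusion.

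Most of this stands, and it limits the claim to a risk. Three things remain. The listed safeguards do not address inference from earlier open allocations. Motivation is assessed without a named instrument, and the timing of inclusion has some slack: rescreening is put at 4 weeks in one section and at 4 to 6 weeks in another. Adjustment for baseline scores corrects only what those scores capture, and motivation may not be among it.

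**Conclusion.** The scheme is more predictable than it needs to be. In complete 1:1 blocks of 4, one third of allocations are certain and the best guess is right 71% of the time. With 5 to 40 care managers assumed, the certain share is about 32% to 25%, or 64 to 50 of 200 patients. These figures hold for an observer who knows the block size and all earlier allocations in the stratum. Whether those who include patients are in that position is neither shown nor excluded.

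A reader might infer that recruiters know the next allocation for 67 of the 200 patients, or that the comparison is already biased. The article supports neither. The first treats an upper bound as a fact and assumes full access to the history. For the second there is no evidence that anyone acted on a prediction, and no size of bias can be derived. The sample size is not affected.

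**What to change.** For all remaining inclusions:

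1. Generate a new list with block sizes of 4 and 6 in random order within each care manager. Withhold the sizes from recruiting staff and care managers.
2. State that the independent researcher who made the list holds the envelopes, and opens each one only when that patient's eligibility and consent have been recorded.
3. State who conducts the eligibility interviews, and that they are not told earlier allocations.

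**Gain.** Certain allocations fall from about one third to about 6%. The best guess improves little, from 71% to about 69%, so points 2 and 3 matter as much as the new list.

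**Cost.** One new computer list, a named envelope holder and a short amendment. Imbalance within a care manager can reach 3 instead of 2, which largely keeps the workload aim. That limit holds if each care manager moves to the new list at the end of the current block.
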